## Abstract

**Background:**

Chronic non-cancer pain (CNCP) is a common condition worldwide. The disease burden is influenced not only by pain itself, but also by psychiatric co-morbidities, which aggravate symptoms, generally negatively influence therapies, and may thereby lead to frustration, resignation, or withdrawal. A growing body of evidence suggests that sex and gender aspects influence CNCP management as the experience of pain, the emotions associated with it, and the expression of pain may differ between women and men. In addition, doctor-patient communication is known to be influenced by gender stereotypes. Despite there being evidence on such differences, current guidelines do not consider sex- and gender-sensitive approaches. In order to examine how to adequately address the diversity of the experience and processing of pain in patients of differing sex and gender, the GESCO study aims at developing and pilot testing a sex- and gender-sensitive intervention for patients with CNCP receiving long-term opioid therapy (LTOT) in primary care.

**Methods:**

The development process is designed in accordance with the first two phases of the UK Medical Research Council. Phase I will iteratively explore, develop, and pilot the intervention’s modules using literature searches, interviews, and workshops involving stakeholders and experts. Phase II will pilot-test the novel intervention in a sample of 40 patients with CNCP under LTOT from ten general practices using an effectiveness-implementation hybrid design including a mixed-methods process evaluation focusing on implementation strategy criteria and a single-arm, pre-post comparison to determine preliminary effects in preparation for a larger effectiveness trial. The intervention will combine in-person educational sessions for general practitioners and tools to be used in patient care.

**Discussion:**

The intervention aims to improve CNCP management in primary care by empowering practitioners to reflect on their attitudes towards pain and stereotypes. Besides sex and gender aspects, awareness of other factors that might affect the care process, such as age, social conditions, or culture, is also promoted. The intention is to develop a comprehensive care concept for CNCP that considers aspects relevant for sex- and gender-sensitive care which are transferrable to other health care fields as well.

**Trial registration:**

German Clinical Trial Register DRKS00029980.

**Supplementary Information:**

The online version contains supplementary material available at 10.1186/s40814-024-01564-7.

## Background

Chronic non-cancer pain (CNCP) is a common condition worldwide, negatively affecting individuals, families, and communities as well as national economies [1–4]. Opioid therapy can significantly improve CNCP symptoms but may also pose a problem in itself [5]. Germany is among the countries with the highest per capita consumption of opioids for CNCP worldwide [6]: in 2012, 1.3% of insured persons received long-term opioid therapy (LTOT). The disease burden in patients with CNCP is influenced not only by pain itself, but also by psychiatric co-morbidities, which commonly aggravate symptoms and are known to hamper therapy [7, 8]. In everyday care, insufficient success of CNCP treatment often results in frustration for both the patient and the therapist and may lead to resignation and withdrawal on one or both sides [9, 10], frequently associated with opioid misuse [9, 11, 12].

A growing body of evidence suggests that CNCP management and co-morbidities are subject to influences associated with sex and gender aspects [13–15]. Gender is a concept considering social, environmental and situational connotations, identity and the role of a person whereas sex refers to the biological function. However, sex and gender do influence each other, which frequently impairs a differentiation between sex- or gender-specific aspects [16]. In medicine, sex and gender differences are well described for many conditions where gender differences in pain perception and coping with pain have been described in animals and humans [17–19]. In pharmacology, sex differences have been described for the pharmacokinetics as well as the pharmacodynamics of many frequently used drugs [20, 21]. Among them are opioids, where a body of evidence supports the hypothesis that gonadal hormones influence and determine sex-specific differences in pain and opioid-associated effects [22, 23].

In the context of chronic pain, sex and gender aspects are relevant not only regarding different prevalences of co-morbidities, but also in terms of experiencing and processing chronic pain itself. Among others, studies report differences regarding pain-related negative emotions such as anxiety and frustration [24], more detailed reporting of negative experiences with their physicians among women [25], and a higher prevalence of childhood trauma and family conflict in women [15]. It is also known that male and female patients with CNCP differ in how they verbally and non-verbally express pain [26] and that health care professionals’ communication is influenced by gender stereotypes [10, 27, 28].

Even though there is evidence on differences between men and women, current clinical guidelines focus on critically reviewing the therapy of patients with CNCP, examining whether opioid prescriptions are adequate and which alternatives might be used instead, but they do not consider any gender-sensitive approaches [29–32].

Despite the recognized importance of gender in doctor-patient communication, most communication skills assessment instruments in medical education neglect this factor, with only a minority incorporating gender-related content. To improve communication training for medical professionals, clearer criteria and purposes for integrating gender considerations into assessment practices are needed [33]. Doing this, it has to be taken into account that beyond the existing research on gender topics, there are still gaps in knowledge regarding the actual magnitude of gender disparities in pain care as well as on which specific interventional strategies might help to adequately address these disparities. Thus, there is a need to participatory develop more targeted group-specific care concepts for patients with CNCP on LTOT that consider a variety of sex- and gender-sensitive approaches. Such approaches should not include stereotypical standard interventions for women and men, respectively, but should increase awareness for stereotypical differences and also enable physicians to address patients in light of other individual factors such as biological, cultural or psychosocial background, which are known to be relevant for CNCP management as well [34]. As the results of dyad research suggest [35], this requires an intervention that includes elements of reflection on the physicians’ subjective attitudes towards pain and gender and their role as practitioners, in addition to improving their (sex- and gender-sensitive) communicative competencies [36]. This approach has the potential to benefit patients by fostering greater empathy and understanding in doctor-patient interactions, ultimately leading to more tailored and appropriate care.

### Objectives

The aims of the study are twofold: The first is to develop a novel gender-sensitive care for chronic non-cancer pain patients receiving long-term opioid therapy (GESCO) intervention to support individuals with CNCP receiving LTOT in primary care. In this step, the elements of the GESCO intervention including implementation strategies required to apply the intervention in the care of patients with CNCP will be developed. The second is to determine the feasibility of this intervention from the perspective of patients with CNCP and their general practitioners (GPs). This feasibility study aims to identify potential refinements to the intervention’s contents and design prior to a larger effectiveness trial, and to determine preliminary effects to estimate effect sizes for a larger trial [37, 38].

## Methods/design

The GESCO intervention will be developed and pilot tested in terms of feasibility criteria in accordance with the two first phases of the UK Medical Research Council (MRC) Framework for developing complex interventions [39, 40]: First, a development and modeling process will be applied in order to iteratively explore, develop, and evaluate the contents and single modules of the sex- and gender-sensitive GESCO intervention by involving stakeholders and experts (phase I). Second, an exploratory mixed-methods study in a clinical sample of 40 patients with CNCP receiving LTOT, who get managed by ten primary care practices that will be educated previously, will be conducted in order to pilot-test the intervention and determine whether the intervention is feasible for a future effectiveness study (phase II) [38, 41]. The study conduct is visualized in Fig. 1.

**Fig. 1 Fig1:**
[figure not shown]
Study flow of the GESCO study

Reporting of the study refers to the SPIRIT checklist [42], but was adapted for reporting the protocol of a feasibility study considering the CONSORT statement for pilot and feasibility trials [41, 43].

### Phase I: development of the GESCO intervention and implementation strategies

#### Study design

Starting with a theoretical phase, the existing literature will be screened for systematic reviews and original studies focusing on sex- and gender-specifics in CNCP related to pharmacological and non-pharmacological treatment, co-morbidities, patients’ needs, and physician–patient communication, as well as social dimensions. Additionally, national and international guideline recommendations for CNCP treatment will be screened to explore whether they provide any sex- and/or gender-specific recommendations. Based on the findings identified in the literature, patients with CNCP and GPs will be interviewed to assess their needs in the light of the current knowledge.

As a starting point for intervention design, the results of the literature review and stakeholder needs assessments (interviews with GPs and patients with CNCP) will be synthesized into a theory of change [44, 45]: During a participatory workshop with patients, physicians and experts (such as psychologists or sociologists), a long-term goal for the intervention will be defined. Based on the long-term goal, short and intermediate intervention outcomes, activities and inputs will be collected. In a second consecutive workshop the results from the first workshop will be specified—including strategies regarding implementation and sustainment of the intervention. Based on the theory of change, intervention materials and documents will be developed and pre-tested in general practices. The evaluation design will also follow the theory of change.

#### Study setting and eligibility criteria

In order to consider GPs’ and patients’ needs alike, both GPs managing patients with CNCP and patients with CNCP themselves aged ≥ 18 years who have received opioid therapy for at least 3 months will be involved in the development of the intervention. As interviews and workshops will be conducted in German, all participants have to possess sufficient German language skills.

#### Sample size and recruitment

A minimum of six GPs and six patients with CNCP will be recruited for the interviews. The interviews will be carried out following the concept of information power until we have sufficient information power for the analysis of our research questions as well as for the generated quality of the dialog [46].

GPs will personally be invited to participate in an interview on their needs to adequately manage patients with CNCP, when they come to attend training sessions for general practice teams offered monthly at Witten/Herdecke University. Additionally, an invitation letter will be distributed via email to practices associated with the Institute of General Practice and Primary Care, Witten/Herdecke University, as teaching and/or research practices.

Patients with CNCP will be approached via teaching and research practices associated with the university Institute of General Practice and Primary Care and via patient representatives supporting the study in the GESCO advisory board.

For both GPs and patients, a balanced gender ratio will be taken into account. GPs and patients who participate in the interviews will also be asked to attend the workshop in order to support the development of the intervention.

#### Data collection methods and data management

Semi-structured interviews with GPs and patients will be conducted in person at Witten/Herdecke University, via telephone, or using a certified video conferencing system. The guidelines, which will be used for structuring the interviews, will address patients’ and GPs’ experiences regarding CNCP management, patients’ wishes related to CNCP care, and GPs’ needs for treating patients with CNCP (Supplementary Material 1 and 2). The interview guides will consider findings from the previous searches. The development will be supported by GP and patient representatives. All interviews will be conducted by researchers who are trained in qualitative methodologies. No individuals other than the interviewed person and the interviewer will be present.

In order to facilitate the analyses, all interviews will be audio-recorded and transcribed verbatim. All statements identifying a person will be anonymized in the transcription process.

#### Data analysis

In order to make the findings of the interviews promptly available for the development of the intervention, analyses of the qualitative data will be performed using rapid qualitative analysis [47]. The coding process will be responsibly managed by two researchers. The resulting themes of the qualitative analysis will be presented to stakeholders in workshops through structured reports and thematic maps. This information will guide discussions on refining and prioritizing elements of the intervention, ensuring it aligns with the qualitative insights from the study.

### Phase II: pilot testing of the GESCO intervention and the implementation strategies

#### Study design

The pilot testing of the newly developed intervention and the strategies used for implementation will be conducted as a hybrid type 2 effectiveness-implementation study and follows the guidance for conducting feasibility and pilot studies for implementation trials according to Pearson et al. This design features simultaneous testing of both (a) the feasibility of implementation and (b) clinical parameters as co-primary aims [38, 48]. In detail, an exploratory, mixed-methods study consisting of the following elements will be conducted:

Mixed-methods process evaluation with predominantly qualitative methods in order to determine whether it is feasible to proceed to an effectiveness trial.Patient-centered pre-post comparison to quantify preliminary interventional effects in order to get a preview of the magnitude the intervention might have and to prepare a subsequent effectiveness trial.

#### Study setting and eligibility criteria

GPs will be eligible for the feasibility study if they manage patients with CNCP in their everyday practice and prescribe opioids for CNCP treatment. Patients will be included if they are at least 18 years old, suffer from CNCP, and have been receiving opioid therapy for at least 3 months. Patients with a clinically relevant malignant primary disease, patients currently receiving medications for opioid use disorder, and those with insufficient German language skills for participation will be excluded. A balanced gender ratio will be considered for both GPs and patients with CNCP.

#### Sample size and recruitment

Ten GPs from different general practices will be recruited for the feasibility study, excluding those practices and GPs that already participated in the development process. Again, GPs will be informed about the study and invited to participate during training sessions at the university and via email distributed to the institutes’ teaching and research practice network. Considering a patient drop-out rate of 20% and a target sample size of 40 patients for the analysis, each of the ten GPs will recruit five patients fulfilling the eligibility criteria defined for the study. This sample size is sufficient to detect, e.g., a mean difference (before and after intervention) of 0.5 on the 10-point-pain scale with a standard deviation of 1 (alpha = 0.05, power = 80%, 2-sided one-sample-*t*-test).

In order to ensure that the patients recruited for the feasibility study will match the eligibility criteria, study team will provide the GPs comprehensive written information and guidelines on how to conduct the feasibility study. To assess fidelity to the protocol, the study team will conduct study monitoring by periodic checks and also provide ongoing support to the GPs, ensuring they understand and adhere to the established procedures. This monitoring will help maintain consistency and compliance throughout the study.

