**Implementation measures addressing the recruitment process**			
Reach	Recruitment of 10 practices for the study successful within 3 months	Documentation sheet, completed by study center	Continuously during practice recruitment and study conduct
	Success of different recruitment strategies applied for GP recruitment		
	Drop outs (GPs and patients)		
	Recruitment of 50 study patients by 10 practices successful within 3 months	Documentation sheet, completed by the practices	Continuously during patient recruitment
	Patients willingness to receive the GESCO intervention/participate in the study	Qualitative interview with GPs	After completing two consultations per study patient (t1)

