**Sustainability of implementation**			
Sustainability	Uptake of intervention	Qualitative interview with GPs incl. the G-NoMAD [53]	After completing two consultations per study patient (t1)
		Written questionnaire incl. the G-NoMAD [53], completed by GP	Simultaneously with last patient-out per practice

**Table 2 Tab2:** Patient-centered clinical outcomes

*Outcome*	*Measure*	*Data collection*	*Date of data collection*		
			*t0*	*t1*	*t2*
Pain	Pain history and progression (German Pain Questionnaire [58])	Self-assessment, completed by patient	x		x
	10-point-pain scale (three scales: acute pain, average pain during the last 4 weeks, and strongest pain within the last 4 weeks)	Telephone interview with patient, conducted by study nurse	x	x	x
Mental well-being	Depression-Anxiety-Stress Scale (DASS) [59]	Self-assessment, completed by patient	x		x
	The Marburg questionnaire on habitual well-being (FW7) [60]				
Quality of life	Veterans RAND 12-Item Health Survey (VR-12) [61]				
Pain medication	Self-reported medication	Telephone interview with patient, conducted by study nurse	x	x	x
	German, nationally standardized medication plan	Assessed by treating physician	x	x	x
Adverse effects of medication	Self-reported adverse effects	Telephone interview with patient, conducted by study nurse	x		x
Satisfaction with information about medication	Satisfaction with Information about Medicines Scale (SIMS) [62, 63]				
Potential opioid medication misuse	Pain Medication Questionnaire (PMQ) [64]				
Perceived stigma due to pain	Internalized Stigma of Chronic Pain (ISCP) [65]^a^				
Disruption of daily life due to pain	Pain Disability Index (PDI) [66]				
Optimism/pessimism	Optimism–Pessimism Short Scale 2 (SOP2) [67]				

*t0* baseline (before intervention); *t1 *2-month follow-up; *t2 *5-month follow-up

^a^German translation by study team

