#### Data analysis

Analyses of the qualitative data will be performed in MAXQDA 2022 [68] using a deductive-inductive approach. To this end, deductive categories will first be defined on the basis of the interview guides. Afterwards, the coding schemes will be continuously developed and refined over time by identifying categories directly from the text material. The coding process will be responsibly managed by two researchers and will include coding sessions with a group of researchers from the GESCO study team, GP representatives, and patient representatives with CNCP.

For quantitative data, descriptive statistics will be performed using IBM SPSS Statistics for Windows [69] in order to measure preliminary effects. Patients’ baseline and follow-up data will be compared by applying a *t*-test for dependent samples, the Wilcoxon test or McNemar’s/the sign test depending on the distribution of the outcome variable. The nominal significance level for analyses will be defined as *p* < 0.05. In addition, confidence intervals will be reported for any quantities estimated.

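### Paired pre-post tests use only complete pairs and cannot use the t1 pain value; if drop-out after t1 follows early response, the preliminary pain change may be overstated

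*Protocol article*

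**What the plan says.** **Sample size and recruitment (Phase II).** The calculation reads "Considering a patient drop-out rate of 20% and a target sample size of 40 patients for the analysis", and "each of the ten GPs will recruit five patients fulfilling the eligibility criteria defined for the study", which makes 50 recruited. Table 1 repeats the figure as a feasibility criterion: "Recruitment of 50 study patients by 10 practices successful within 3 months". The 40 are said to suffice for "a mean difference (before and after intervention) of 0.5 on the 10-point-pain scale with a standard deviation of 1" ("alpha = 0.05, power = 80%, 2-sided one-sample" t-test).

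**Data analysis (Phase II).** Patients' "baseline and follow-up data will be compared by applying a" dependent-samples t-test, a Wilcoxon test, or McNemar's or the sign test, with confidence intervals. The section does not say which follow-up visit is meant, and it names no method that takes three visits together.

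**Table 2.** The "10-point-pain scale (three scales: acute pain, average pain during the last 4 weeks, and strongest pain within the last 4 weeks") is marked at t0, t1 (2 months) and t2 (5 months). Most other patient outcomes are marked at t0 and t2 only.

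**Data collection and data management (Phase II).** The data for the pre-post comparison are placed at baseline and 5 months. The 2-month contact is described as a qualitative interview plus changes in medication. The pain scale is not mentioned there.

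**Outcomes and Discussion.** The preliminary effect feeds the effect size for a later, larger trial, together with clinical relevance and results from other studies.

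**The concern.** A paired test needs both members of each pair. Read with the data collection section, the natural comparison is t0 with t2, so a patient with pain recorded at t0 and t1 but not at t2 adds nothing to it. Table 2 nevertheless schedules the t1 value that could tell us how such patients were doing when last seen.

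This matters if loss between t1 and t2, a gap of about three months, is related to early response. The observed pairs would then over-represent patients who had already improved. With a single arm, no control group has similar attrition that might offset the selection, so it passes directly into the pre-post change. That change is one of the quantities the study exists to supply.

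**Working it through.** Improvement is counted as positive throughout.

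**1. The plan's own figure.** Inputs from the sample size section: difference 0.5, SD 1 (read as the SD of the paired difference, since a one-sample test is named), two-sided alpha 0.05, power 80%. Power comes from the noncentral t distribution with n − 1 degrees of freedom and noncentrality (0.5/1)·√n.
- The smallest n reaching 80% is 34 (power 80.8%).
- At n = 40 the power is 86.9%.
- 40/(1 − 0.20) = 50 = 10 × 5.

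The stated figures are reproduced and sound.

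**2. How many patients the tests use.** 50 × 0.8 = 40 expected pairs; the other 10 contribute nothing to a t0–t2 test.

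**3. Simple bounds.** The documents give no outcomes for drop-outs, so these are assumptions. Mean change in all 50 = 0.8 × (completers' change) + 0.2 × (drop-outs' change). With completers at 0.5:
- drop-outs also at 0.5: 0.40 + 0.10 = 0.50, no bias;
- drop-outs at 0: 0.40 + 0 = 0.40, completers too high by 0.10;
- drop-outs at −0.5: 0.40 − 0.10 = 0.30, too high by 0.20.

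**4. Drop-out after t1 that depends on early change.** Let X be the standardised improvement from t0 to t1. The log-odds of loss before t2 are a − bX, with a set so that 20% are lost. Then

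bias of the completer mean = SD of change × ρ × E(X | stays),

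where ρ is the correlation between the t0–t1 and t0–t2 changes:

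ρ = (1 + r12 − r01 − r02) / (2·√[(1 − r01)(1 − r02)]).

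Numerical integration gives E(X | stays) = 0, 0.096, 0.173 and 0.262 for b = 0, 0.5, 1 and 2. With the protocol's SD of change of 1 and assumed correlations of 0.6 to 0.7:

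| r01, r12, r02 | ρ | b = 0 | b = 0.5 | b = 1 | b = 2 |
|---|---|---|---|---|---|
| 0.6, 0.6, 0.6 | 0.500 | 0 | 0.048 | 0.087 | 0.131 |
| 0.7, 0.7, 0.7 | 0.500 | 0 | 0.048 | 0.087 | 0.131 |
| 0.7, 0.7, 0.6 | 0.577 | 0 | 0.056 | 0.100 | 0.151 |
| 0.6, 0.7, 0.6 | 0.625 | 0 | 0.060 | 0.108 | 0.164 |

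These are the patterns in which the two most distant visits correlate no more strongly than adjacent ones, and t1–t2 at least as strongly as t0–t1. The range is about 0.05 to 0.16. Other combinations of 0.6 and 0.7 can start lower, at 0.03, and none exceeds 0.16.

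If each pain score had an SD of 2 (an assumption, not the protocol's figure), the SD of change at r02 = 0.6 is 2·√(2 × 0.4) = 1.79. The third row then becomes 1.79 × 0.056 = 0.10 up to 1.79 × 0.151 = 0.27.

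**5. What using t1 achieves.** In simulated studies of 50 patients under step 4, a likelihood-type estimate that lets t0 and t1 inform a missing t2, with unrestricted covariance, returns 0.50 for a true 0.50. At SD of change 1 its standard error is 0.15 to 0.16, the same as for complete pairs. A random-intercept (compound-symmetry) covariance corrects less well, giving 0.51 to 0.57 across the scenarios, so the covariance choice matters.

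**6. What it cannot achieve.** If the 20% with the worst t2 change are lost, the completer bias is φ(0.842)/0.8 = 0.280/0.8 = 0.35 points. Using t1 removes only part of that.

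**7. Possible effect on planning.** Sample size for a mean difference varies as 1/δ². If the inflated change were used directly, the later trial would be sized at (0.50/0.55)² = 83% down to (0.50/0.66)² = 57% of what the true change requires.

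**The case against.** The strongest reply is that this is an exploratory single-arm feasibility study, and that handling of missing values is something a condensed article leaves to the full protocol or SAP. That stands as far as it goes: the absence of a missing-data rule here is not a defect. What remains is the choice the article does state, namely tests that by construction cannot use a third visit.

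Several stronger readings are tempting and not supported:
- **That the estimate is biased.** Nothing in the documents shows that drop-out will be related to outcome. If drop-outs change as completers do, the bias is zero.
- **That the plan excludes patients by rule, or analyses 40 of 50 treated.** The 40 is a planning figure after expected loss. Fifty are recruited, and some may leave before any counselling session.
- **That the sample size sentence is wrong.** It reproduces, with margin.
- **That t1 pain is known to be discarded.** The Data analysis section does not name the follow-up visit, and Table 2 and the data collection text disagree on whether t1 pain exists.
- **That a mixed model cures the problem.** Step 5 places all loss after t1 and makes it depend only on observed change, where such a model works by design. A patient who leaves during the sessions because of the intervention itself may have no t1 value.

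It is also fair that the largest bias in step 4, 0.16, is about one standard error of the completer mean (1/√40 = 0.158). The Discussion says that planning will also use the standard deviation and literature data. This softens the consequence. It does not remove it, because sampling error is shown by the confidence interval and selection is not.

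**Conclusion.** The point holds in conditional form. The named tests use about 40 of 50 recruited patients at the planned drop-out and cannot draw on t1 pain. Should loss after t1 follow early response, the preliminary change would be overstated by about 0.05 to 0.16 points on 0.5 (10% to 32%). This rests on the protocol's SD of 1, assumed correlations of 0.6 to 0.7 and assumed log-odds slopes of 0.5 to 2 per SD of early change. With no such dependence there is no bias, and a three-visit model loses no precision. The t1 argument applies to the pain scales only; it does not reach outcomes scheduled at t0 and t2 alone. The disagreement between Table 2 and the data collection text on t1 pain is certain whatever drop-out does, and it must be settled first.

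**What to change.** 1. Reconcile Table 2 (pain scale at t0, t1 and t2) with the Phase II data collection section (t1 as a qualitative interview plus medication changes), and state whether t1 pain is collected.
2. If it is, replace the paired tests for the three pain scales with one repeated-measures mixed model per scale in all recruited patients with baseline data: visit as fixed effect, unstructured covariance within patient, GP as random effect. Report t2 versus t0 with its confidence interval.
3. For outcomes measured only at t0 and t2, keep the paired tests. Add the baseline values of completers and drop-outs side by side, and one sensitivity analysis assuming no change in drop-outs.
4. State the limit: the model corrects only for loss explained by observed t0 and t1 values, not for patients lost before t1 or for loss that depends on unseen t2 values.

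The cost is analysis wording and a little programming. No new data are needed if t1 pain is collected as Table 2 shows, and the recruitment target is unchanged.
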